## Abstract

Artificial intelligence (AI) is entering surgical planning along a continuum that runs from imaging assistance to near-autonomous plan generation, and facial reconstructive surgery—where outcomes bear directly on identity and social functioning—is among the most sensitive settings for this transition. Existing acceptability research has largely compared AI-supported care with conventional care in binary designs, and Central and Eastern European populations remain underrepresented. This protocol describes a cross-sectional, within-subjects vignette experiment among Romanian adults recruited online (target *N* = 300 valid responses; minimum analyzable *N* = 140, raised by a pre-registered rule if the pilot’s inter-scenario correlation falls below the planning assumption). Each participant will read four hypothetical scenarios describing progressively autonomous AI involvement in facial reconstructive surgical planning: imaging assistance, decision support, outcome simulation, and autonomous planning. Participants are randomly allocated to one of the four sequences of a Williams balanced Latin-square design, so that the autonomy level is orthogonal to serial position and to first-order carry-over. After each scenario, they will rate acceptability, trust, and perceived risk (three seven-point Likert items each), responsibility attribution across four loci (surgeon, hospital, AI developer, unavoidable medical uncertainty), perceived AI control and perceived technical sophistication (manipulation checks), and scenario difficulty. Primary analyses are mixed repeated-measures ANOVAs with presentation sequence as a between-subjects factor, orthogonal polynomial (linear, quadratic, cubic) trend contrasts, and Holm-corrected pairwise comparisons, complemented by a position-adjusted linear mixed model; secondary analyses address responsibility migration and concentration, moderation by AI familiarity, and global implementation preferences. A pilot study (*N* = 50, allocated 1:1 to the ascending and descending sequences) will establish reliability, factor structure, comprehension, manipulation validity, and a first bound on order effects before pre-registration on the Open Science Framework and the start of data collection.

## 1. Introduction

### 1.1. Background

Artificial intelligence (AI) applications have expanded rapidly across plastic and reconstructive surgery, with systematic reviews documenting uses that span diagnosis, preoperative planning, intraoperative support, and outcome prediction [1,2,3]. Facial plastic and reconstructive surgery accounts for many of the most mature examples [4,5]. Deep learning systems now segment craniofacial structures on computed tomography (CT) with expert-level accuracy [6], localize three-dimensional cephalometric landmarks automatically [7], and quantify bone properties such as mineral density opportunistically from routine CT [8]. Beyond image analysis, AI models generate candidate surgical plans from cephalometric data [9], automate donor-site segmentation for virtual planning of facial reconstruction [10,11], and simulate three-dimensional postoperative facial appearance before an operation is performed [12,13]. At the far end of the continuum, autonomous robotic systems have completed soft-tissue surgical tasks under minimal human control in preclinical settings [14], and frameworks now grade surgical AI and robotic systems by their levels of autonomy, from passive assistance to conditional autonomy [15,16], with staged evaluation pathways proposed for their clinical introduction [17].

Facial reconstructive surgery is a particularly consequential setting for this transition. Because the face is central to personal identity, social interaction, and psychological well-being, decisions about facial reconstruction carry stakes that extend beyond function, and ethical analyses of AI in facial surgery emphasize consent, privacy, and the special status of facial data [18]. Whether progressively autonomous planning systems are adopted will depend not only on technical performance but also on their acceptability to prospective patients: attitudes, trust, perceived risk, and beliefs about who bears responsibility when errors occur shape patients’ willingness to consent, clinicians’ willingness to rely on algorithmic outputs, and the regulatory conditions under which such systems operate [19,20].

### 1.2. Public Attitudes Toward Medical AI

A substantial body of the recent literature has characterized public and patient attitudes toward clinical AI. Syntheses converge on a consistent pattern: the public is broadly receptive to AI as a support tool but insists on human involvement and personalized care [21,22]. Large surveys find that most patients expect AI to improve care while reporting substantial concerns about misdiagnosis, privacy, and the erosion of the patient–clinician relationship [23], that comfort is conditional on physician supervision of the final decision [24,25], and that trust is lowest precisely for surgical applications [26]. Experimental work shows that acceptance of AI-based care rises when physicians endorse and explain the system [27,28], and that patients react negatively when AI use is not disclosed or when AI and clinician recommendations conflict [29,30]. A recent multinational hospital survey spanning 43 countries confirmed predominantly favorable views combined with a marked preference for explainable, physician-supervised AI [31]. Within surgery specifically, patients presenting to a surgical clinic reported low familiarity with and limited trust in AI involvement in their care [32], and users evaluating AI-enabled decision aids valued them for shared decision-making rather than autonomous decision-making [33]. Vignette-based population experiments identify system reliability and transparency as the leading drivers of support [34], and AI familiarity, education, and health literacy recur as determinants of acceptance [35,36].

### 1.3. Trust, Algorithm Aversion, and Responsibility

Two research streams supply the study’s theoretical structure. The first concerns algorithm aversion and appreciation: systematic reviews and integrative syntheses show that lay evaluations of algorithmic advice depend on the task, the decision stakes, the visibility of algorithmic error, and the degree of human control retained, with aversion most pronounced in consequential, subjective, or embodied domains [37,38]. In medicine, reluctance to rely on algorithmic care has been traced in part to an illusory sense of understanding of human decision-making relative to algorithmic decision-making, and it can be attenuated by explanation [28]; explainability, however, is not sufficient on its own, since explanation quality can either build or erode trust [39]. Trust research in healthcare AI—for both the public and clinicians—identifies perceived reliability, transparency, workflow fit, and accountability as recurring determinants [19,40].

The second stream concerns responsibility for AI-involved errors. Surveys show the public predominantly holds physicians responsible for harms arising in AI-assisted care, while physicians more often assign liability to developers and institutions [41]; experimental work with mock jurors indicates that clinicians who follow standard-of-care AI advice are not judged more harshly [42], and that institutions attract greater blame after AI-involved adverse events unless clinicians visibly engage with the system’s outputs [43]. Conceptual analyses describe how causal, moral, and legal responsibility diffuse across clinicians, developers, and institutions in AI-supported care—the “problem of many hands”—and warn of emerging responsibility gaps [44,45]. Normative work argues that the clinician’s role in the loop should amount to substantive co-reasoning rather than nominal veto power [46,47], a position echoed by the human-oversight obligations that the EU Artificial Intelligence Act imposes on high-risk systems [20,48]. The evolving European liability landscape—including gaps identified in the proposed AI liability directives and the reconfiguration of the doctor–patient relationship under the AI Act—makes the allocation of responsibility for surgical AI a live regulatory question [49,50,51]. However, empirically, how laypeople re-allocate responsibility as AI autonomy increases has scarcely been quantified, particularly with within-person designs; a recent vignette study among physicians found that they retained personal moral responsibility while endorsing institutional co-responsibility [52], but comparable public data along a graded autonomy continuum are lacking.

### 1.4. Adjacent Consumer-Facing Health AI: Capability Advances and the Acceptability Lag

A third body of work, published largely in engineering rather than health-services venues, sets the technical horizon against which public attitudes must be read, and shows why acceptability evidence lags capability. Hu et al. [53] use global and marginal contrastive clustering to recognize faces in partially aligned, multi-view consumer-device data, achieving robust identification where views are incomplete or unpaired. This is the same class of representation that makes automated craniofacial analysis feasible outside a controlled radiology setting, an indication of how readily facial data captured on ordinary consumer devices can be organized and matched at scale. Yang et al. [54] describe a consumer-centric digital-twin framework for coronary artery disease in which a continuously updated patient model performs risk stratification and generates individualized management proposals, with explainability layered over the predictions. Structurally, this is our Scenario D—a machine-generated plan that a clinician reviews rather than composes—transplanted to cardiology; plan generation is therefore being engineered for consumer-facing deployment across specialties, not confined to surgical research settings. Yang et al. [55] address the layer beneath both, using reinforcement learning with adversarial data augmentation to detect distributed denial-of-service attacks against connected consumer healthcare devices; the availability and integrity of that layer are preconditions for any clinical claim built on top of it, and they are also, in the patient’s view, part of what is being trusted.

Read together, these studies establish that the capability frontier—biometric facial representation, autonomous plan generation, and the connected infrastructure that carries both—is advancing fastest on the consumer side, where devices and data leave the clinical setting, and the person concerned has the least oversight. What none of them establish, and what remains unresolved, is whether the people whose faces, physiology, and devices are involved regard these arrangements as acceptable, whom they hold responsible when such systems err, and at which point along the autonomy continuum their acceptance breaks down. Technical validation is reported as accuracy against benchmarks and as robustness under attack; acceptability is a distinct empirical quantity with its own measurement requirements, and it cannot be inferred from either. Two consequences follow for the present protocol. First, the autonomy levels examined here are not speculative: each corresponds to a capability already realized or under active development, so the attitudes measured are attitudes toward systems that patients may encounter. Second, the design isolates the quantity the technical literature leaves unmeasured—it holds the clinical task constant, varies only the degree of machine autonomy, and records acceptability, trust, perceived risk, and responsibility attribution within person, so that the location and shape of any decline in acceptance can be estimated rather than assumed.

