
### 2.2. Experimental Vignettes

The four vignettes describe distinct configurations of AI involvement in facial reconstructive surgical planning, varying both the AI’s task (imaging analysis, decision support, outcome simulation, autonomous planning) and the surgeon’s level of supervision (Table 1). Each configuration corresponds to a capability documented in the current literature: anatomical structure analysis from CT [6,8], algorithmic generation of candidate surgical plans [9], three-dimensional simulation of postoperative facial appearance [12,13], and highly autonomous planning of the kind anticipated by surgical-autonomy frameworks [14,15]. All vignettes open with an identical premise (the respondent needs facial reconstructive surgery following an injury) and are written in parallel second-person wording of comparable length and reading difficulty, so that scenario content—not framing—drives differences in responses. Because the four configurations differ in what the AI does as well as in how much the surgeon decides, a perceived difference between them could in principle reflect technical sophistication rather than autonomy. Three features are intended to keep the two apart. First, every vignette closes by stating explicitly how the final surgical plan is reached and by whom. In Scenarios A–C, a single clause of parallel construction names the surgeon as the decision-maker (making all decisions, choosing among the proposed options, or deciding the final plan after reviewing the simulations); in Scenario D, the closing sentences state that the surgeon reviews the AI’s plan but rarely modifies it. What varies is therefore the decisional locus, not the computational task. Each comprehension check is built on that same feature: the decision-maker in Scenarios A and B; the role of the system in Scenario C (whose decisional clause is functionally equivalent to Scenario B’s, so that the role is what distinguishes the two); and the origin of the plan actually followed in Scenario D. Second, the vignettes are matched on the quantity of technical detail supplied—one sentence describing the system’s input and output in each case—so that described sophistication does not rise in step with autonomy. Scenario C specifies a generative three-dimensional simulation, computationally the most elaborate output in the set, yet leaves the decision entirely with the surgeon; Scenario D describes a comparatively conventional optimization whose distinguishing feature is decisional rather than technical. Third, two manipulation checks follow every scenario: MAN1, perceived control of the AI over the final decision, and MAN2, perceived technical sophistication of the system. The manipulation is treated as valid only if MAN1 orders the scenarios as intended; MAN2 verifies that sophistication does not itself increase monotonically with autonomy and enters a pre-specified sensitivity analysis as a covariate, so that the autonomy effect can be estimated with perceived sophistication held constant (Section 2.9.1). The full vignette texts are provided in Appendix A.

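### The vignettes change the AI's task together with the surgeon's supervision, so the plan cannot say that only autonomy varies, and a B–C difference cannot locate an autonomy break

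*Protocol article*

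**What the plan says.** Section 1.4 presents the design as isolating autonomy: "it holds the clinical task constant, varies only the degree of machine autonomy".

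Section 2.2 opens by describing the vignettes as "varying both the AI’s task (imaging analysis, decision support, outcome simulation, autonomous planning) and the surgeon’s level of supervision". Table 1 agrees: the AI's role differs in every row (highlighting anatomy, proposing three plans, simulating appearance, producing a complete plan), and so does the surgeon's role. Section 2.2 then acknowledges that "the four configurations differ in what the AI does as well as in how much the surgeon decides", and takes the resulting risk to be that a difference "could in principle reflect technical sophistication rather than autonomy. Three features are intended to keep the two apart". After describing the closing clauses of the vignettes it concludes: "What varies is therefore the decisional locus, not the computational task".

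The checks are MAN1 ("The manipulation is treated as valid only if MAN1 orders the scenarios as intended") and MAN2, which enters a sensitivity model "so that the autonomy effect can be estimated with perceived sophistication held constant". Section 2.2 also says that the clause on who decides does the same job in C as in B, and for that reason builds C's comprehension check on the system's role instead.

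Section 2.9.1 tests H1 and H2 by polynomial trend contrasts over A to D and identifies any break from the adjacent pairs A–B, B–C and C–D. The seven limitations in Section 4 do not include confounding of task with autonomy.

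**The concern.** The statements in 1.4 and at the end of the closing-clause argument in 2.2 cannot stand beside the opening of 2.2 and Table 1. The design lacks a property that the protocol claims for it.

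This matters for inference. H2 says that perceived risk rises as human control falls. If respondents rate a scenario as riskier because of what the AI does there, with the surgeon's control unchanged, the planned tests would report that as support for H2. The same holds for H1 and for the scenario × actor interaction that tests H3. Counterbalancing does not help, because it balances order and not content. The B–C step is the plainest case: by the protocol's own account the stated decisional role is equivalent there while the AI's task changes, yet B–C is one of three contrasts used to say where acceptance breaks.

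**Working it through.** **The texts side by side.** Section 1.4: only autonomy varies. Section 2.2, opening, and Table 1: AI task and supervision both vary. Section 2.2, later: the decisional locus varies and the computational task does not. The second statement contradicts the first and third. With four scenarios for four levels (Section 2.1), knowing the level means knowing the task, so no degree of freedom is left to estimate one given the other.

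**The plan's own figures.** Inputs from Section 2.5: m = 4 levels, ρ = 0.50, two-sided α = 0.05, N = 300. With λ = f²·N·m/(1 − ρ) and 3 and 3(N − 1) degrees of freedom, the noncentral F distribution gives a minimum N of 138 for f = 0.10 and power 0.991 at N = 300. Both match the protocol (138 and 0.99).

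**The same sensitivity applied to task content.** Let the true autonomy effect be zero, and let each vignette carry its own mean shift with SD τ in units of the rating SD. τ is an assumption; the documents give no value.

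- Linear contrast (−3, −1, 1, 3), sum of squares 20.
- Sampling variance: 20(1 − ρ)/N = 20 × 0.5/300 = 0.0333.
- Content variance: 20τ². For τ = 0.10 this is 0.20.
- Total over sampling variance: 1 + Nτ²/(1 − ρ) = 1 + 300 × 0.01/0.5 = 7.00.
- Rejection rate: P(|Z| > 1.963/√7.00) = P(|Z| > 0.742) ≈ 0.458.

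| Assumed τ | Variance ratio | Linear trend significant, ρ = 0.50 | Same, ρ = 0.30 |
|---|---|---|---|
| 0 | 1.0 | 5.0% | 5.0% |
| 0.05 | 2.5 | 21.5% | 17.3% |
| 0.10 | 7.0 | 45.8% | 39.4% |
| 0.20 | 25.0 | 69.5% | 64.5% |

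The variance ratios are for ρ = 0.50. A simulation of 4,000 studies at τ = 0.10 and ρ = 0.50 gave 46.2%. By symmetry half of the rejections fall in the predicted direction: 22.9% at τ = 0.10. A larger sample does not protect: at τ = 0.10 and ρ = 0.50 the rate is 31.4% at N = 140 and 45.8% at N = 300.

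**A fixed effect on one vignette.** This version treats no scenario as a random draw (N = 300, ρ = 0.50).

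- A task effect of 0.10 SD on D alone: contrast 3 × 0.10 = 0.30, SE √0.0333 = 0.183, ratio 1.64; the linear trend is significant in 37.5%. At 0.20 SD it is 90.7%.
- A task effect of 0.20 SD on C alone: the linear trend is significant in only 19.4%. For B–C, dz = 0.20/√(2 × 0.5) = 0.20, detected in 93.2% without correction. At the Bonferroni bound, Section 2.5 itself gives dz = 0.20 as detectable with power 0.80. A modest task effect in C would therefore usually be reported as a break at B–C.

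**The case against.** Several replies have force. In 1.4, the clinical task may mean the shared injury premise, which is constant; but the claim that only autonomy varies fails even so. The sentence "What varies is therefore the decisional locus, not the computational task" follows the account of the closing clauses and could be read as being about those clauses alone; as written it speaks of the design, and Table 1 contradicts it. The full vignette texts are not in the material at hand, so what differs in content is taken from Table 1 and Section 2.2.

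A reader might infer that sophistication is the only thing guarded. The documents do not support that: there are also an identical premise, parallel wording, explicit decision clauses, comprehension checks and MAN1. These show that perceived control is ordered and understood. They do not show that nothing else changed. If MAN1 put C above B, that difference would itself arise where the stated decisional role is equivalent and the task is not.

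A reader might also infer that a contrast of D with the mean of A–C would isolate autonomy. It would not, because D has its own task. Under random content it rejects as often as any other contrast of the four means. With a 0.10 SD content effect on D alone, the contrast is 0.10 with SE √((4/3) × 0.5/300) = 0.047, ratio 2.12, significant in about 56% against 37% for the linear trend.

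Nor do the documents support reading all differences among A, B and C as task differences only. Table 1 gives the surgeon different scope in A (interprets independently, makes every decision) and B (selects from AI proposals). Only B and C are called equivalent.

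Finally, the four scenarios were chosen deliberately and the primary objective concerns these four, so fixed-scenario error is suitable for comparing them. That stands, and it is why the conclusions should be worded as comparisons of configurations.

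**Conclusion.** The protocol is wrong as written in 1.4 and in the later sentence of 2.2. The contradiction and the complete aliasing of task with autonomy rest on the text and need no assumption. So does the point on B–C: a difference there cannot be read as an autonomy threshold.

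The size of the distortion is not known. The rate of about 46% is illustrative. It rests on an assumed content SD of 0.10, of the same order as the plan's small effect, with no autonomy effect, N = 300 and ρ = 0.50. It ranges from about 17% to 70% over content SDs of 0.05 to 0.20 and ρ of 0.30 to 0.50. It shows that a task effect can appear as an autonomy trend, not that it will. The planned comparisons between the four scenarios remain valid as such; their attribution to autonomy alone is not supported.

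**What to change.** Before pre-registration:

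1. In Sections 1.4 and 2.2, replace the two sentences with a statement that AI task and surgeon supervision vary together across the four configurations.
2. In Sections 3 to 5, word H1–H3 conclusions as differences between these four configurations, not as effects of autonomy alone. Sections 3 and 5 already speak of implementation configurations in places.
3. In Section 2.9.1, state that a B–C difference is not evidence of an autonomy break, because the stated decisional role is equivalent in the two scenarios.
4. In the Section 4 limitations, add that task and autonomy are confounded with one vignette per level, and that MAN1 and MAN2 do not separate them beyond perceived control and perceived sophistication.

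No new data, sample size or test is needed. The cost is narrower causal wording about autonomy. Separating the two factors would take a different design, with several vignettes per level or task crossed with decisional role; that is a matter for a later study.

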### 1.5. Knowledge Gaps and Rationale

Three gaps motivate the present protocol. First, most acceptability studies compare AI-supported care with conventional care in binary designs [21,22]; such designs cannot reveal where along the continuum from assistance to autonomy acceptance begins to erode, whether the decline is linear or threshold-like, or how trust, risk perception, and responsibility attribution reconfigure across intermediate levels of autonomy of the kind now documented in facial surgical planning [9,13,15]. Second, the evidence base is geographically skewed toward North America, Western Europe, and East Asia [21,31]. Central and Eastern Europe is sparsely represented: the available regional studies concern physicians’ perceptions in Romania [56,57], Romanian medical students [36,58], and general or patient populations in Poland [59,60]; none examines graded surgical AI autonomy in a general adult population. Attitudes in this region cannot simply be extrapolated from findings elsewhere, given differences in health-system experience, institutional trust, and digital-health exposure [59,60]. Third, and cutting across both, the acceptability evidence has not kept pace with the capability frontier reviewed in Section 1.4: the forms of AI involvement whose acceptability is least well characterized—machine-generated plans reviewed rather than composed by a clinician, built on facial data captured and carried by consumer devices—are precisely those now being engineered for deployment [53,54,55], so the interval between technical feasibility and evidence on public acceptance is widening rather than closing.

